### 2.6. Outcome Measures

The primary outcome of the protocol is the change in pain intensity, measured by the Brief Pain Inventory—Short Form (BPI), from the beginning of the study (T1) to the eight-week follow-up (T3). The item “worst pain in the last 24 h” (numerical scale from 0 to 10) will be used as the indicator of pain intensity, as it has been validated and demonstrated to be clinically important in oncology and palliative care populations.

Secondary outcomes will encompass metrics designed to assess the psychological, functional, and symptomatic domains. Psychological morbidity will be assessed using the Hospital Anxiety and Depression Scale (HADS), including total and subscale scores. Quality of life will be evaluated using the McGill Quality of Life Questionnaire.

In addition to longitudinal assessments at T1 (baseline), T2 (four weeks), and T3 (eight weeks), the immediate pre- and post-intervention effects will be explored using the Edmonton Symptom Assessment Scale (ESAS). The ESAS will be administered prior to and following each in-person guided meditation session to assess acute changes in symptoms. Pain intensity, severity, and interference will be measured using the respective subscales of the BPI. The extent to which participants adhere to the intervention will be determined by calculating the percentage of prescribed meditation sessions completed during the follow-up period.

The subsequent Table 3 offers a synopsis of all outcome measures, variables, analysis metrics, aggregation methods, and assessment time points.

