### 3.2. Analysis

Descriptive statistics are applied to characterize patients at baseline. Continuous variables are reported as the mean and standard deviation, while categorical variables are expressed as frequency and percentage. To analyze the longitudinal data of the three groups, repeated-measures ANOVA is used to define the impact of each intervention on the three paired groups of participants. The response variable, which is mindfulness meditation through virtual reality, is analyzed over time, comparing the three groups. If we do not have a normal sample, we will perform the analysis of Generalized Estimating Equations (GEEs), a semi-parametric method to test the differences between groups and the interaction of variables and groups over time.

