While the existing literature demonstrates the benefits of VR in chronic pain contexts, with significant reductions in pain intensity, psychological distress, and functional disability, the present protocol seeks to expand this discussion of evidence to a scenario that has been little explored: cancer pain in palliative care [25,26].

Another aspect to consider is the emotional and psychological state of patients. Evidence indicates that emotional distress acts as a modulator of pain perception and response to non-pharmacological interventions [9]. Meditation can promote significant improvement in quality of life, as demonstrated even in populations with high psychological morbidity [10,23]. However, for these benefits to remain consolidated, continuous practice is essential, which makes adherence a critical variable.

Moreover, the extant literature acknowledges that in randomized trials, equivalence of duration between groups is not a methodological requirement. Consequently, these groups are capable of participating in sessions of varying durations, as the duration of interventions is no longer regarded as a limitation, in contrast to conventional mindfulness programs [26]. Studies have demonstrated that there are no substantial discrepancies between the short-term and long-term consequences of interventions that utilize brief meditation techniques to enhance well-being [27].

This scenario should be carefully considered in the final analysis of the results, since differences observed between modalities may reflect both the intrinsic effectiveness of each meditation format and the ability of each patient to maintain the proposed practice. Future research should explore strategies to optimize adherence, such as active remote support, hybrid sessions (in person and at home), or personalized adaptations to the patient’s clinical profile.

It is important to note that this protocol is vulnerable to certain limitations, particularly in cases involving patients receiving palliative care in the terminal phase of the disease. These limitations may include loss to follow-up due to death, the emergence of uncontrollable pain from disease progression, and the combination of pharmacological therapies such as chemotherapy, which can cause side effects and symptoms that are complex to manage.

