## Figures and Tables

**Figure 1 healthcare-14-00266-f001:**
[figure not shown]
Flowchart of the experimental design.

**Table 1 healthcare-14-00266-t001:** Temporal implementation of the experimental protocol.

Planning (0–1 Year)	Intervention (1–2.5 Years)
Questionnaire preparation Definition of criteria Patient selection Randomization and sample size Group allocation	Informed consent (TCLE) Initial questionnaire Assessments at 3 time points Meditation protocol Edmonton Symptom Scale

**Table 2 healthcare-14-00266-t002:** Descriptive table of the experimental groups; time of the experimental protocol; and instruments applied.

Group	Time	Study Assessment Instruments
Case group (Group A) Virtual reality/3D (VR)	Time 1 (T1)—First Day of Intervention	
	Before Meditation	Sociodemographic and clinical questionnaire McGill Quality of Life Questionnaire [17] Brief Pain Inventory (Short Form) [18] Hospital Anxiety and Depression Scale [19] The Edmonton Symptom Assessment Scale (ESAS) [20] The National Comprehensive Cancer Network^®^ (NCCN) [21]
	After Meditation	The Edmonton Symptom Assessment Scale (ESAS) [20]
Active Control Group (Group B) Guided Meditation 2D Video	Time 2 (T2)—Four Weeks After T1	
	Before Meditation	McGill Quality of Life Questionnaire [17] Brief Pain Inventory (Short Form) [18] Hospital Anxiety and Depression Scale [19] The Edmonton Symptom Assessment Scale (ESAS) [20] The National Comprehensive Cancer Network^®^ (NCCN) [21]
	After Meditation	The Edmonton Symptom Assessment Scale (ESAS) [20]
Passive Control Group (Group C) Audio-guided meditation—Audio for breathing exercises	Time 3 (T3)—Eight Weeks After T1	
	Before Meditation	McGill Quality of Life Questionnaire [17] Brief Pain Inventory (Short Form) [18] Hospital Anxiety and Depression Scale [19] The Edmonton Symptom Assessment Scale (ESAS) [20] The National Comprehensive Cancer Network^®^ (NCCN) [21]
	After Meditation	The Edmonton Symptom Assessment Scale (ESAS) [20]

**Table 3 healthcare-14-00266-t003:** Overview of outcome measures and analytical framework.

Outcome	Measurement Variable	Analysis Metric	Aggregation Method	Time Points
Primary outcome	BPI: “worst pain in the last 24 h” (0–10)	Change from baseline; final value	Mean (SD); mean difference	T1, T2, T3
Psychological morbidity	HADS total and subscales	Change from baseline	Mean (SD)	T1, T2, T3
Quality of life	McGill Quality of Life Questionnaire scores	Change from baseline	Mean (SD)	T1, T2, T3

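### Section 3.2 fixes repeated-measures ANOVA with an undefined normality switch to GEE; this fits the expected attrition badly and does not isolate the T1–T3 contrast in worst pain

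*Protocol article*

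**What the plan says.** Protocol article, Section 3.2, is the only analysis text in the document. For the longitudinal data it states that "repeated-measures ANOVA is used to define the impact of each intervention on the three paired groups of participants". It then says "The response variable, which is mindfulness meditation through virtual reality, is analyzed over time, comparing the three groups". The alternative is conditional: "If we do not have a normal sample, we will perform the analysis of Generalized Estimating Equations (GEEs"). That method is meant "to test the differences between groups and the interaction of variables and groups over time". No T1–T3 contrast appears in the section.

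Section 2.6 sets the primary outcome as change in the BPI worst-pain item "from the beginning of the study (T1) to the eight-week follow-up (T3"). Table 3 gives two metrics for it, "Change from baseline; final value", and lists all three time points.

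Section 3.1 names SPSS 29.0 and three measurements, calls attrition in this setting high, and adds 12% to 39 per group to reach 43. The limitations in Section 4 include "loss to follow-up due to death, the emergence of uncontrollable pain from disease progression".

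**The concern.** Four features of the stated method work against the stated endpoint.

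- **Missed visits.** Classical repeated-measures ANOVA, as run by the usual SPSS routine, needs a value at every visit. A patient who misses T2 or T3 leaves the analysis, together with whatever was observed. In a palliative population the patients lost are unlikely to be a random subset.
- **The switch.** The normality condition does not say what is tested, how, or at what threshold. It leaves two possible results for the primary outcome. Normality also does not decide how missed visits should be handled. GEE keeps observed visits, but without weighting it generally needs losses to be completely at random.
- **The contrast.** The group main effect averages in T1, which precedes the intervention. The omnibus group-by-time interaction responds to any departure from parallel profiles, including one at T2 only. Neither is the T1–T3 comparison.
- **The wording.** The response variable is given as the intervention rather than worst pain, and three independently randomized arms are called paired.

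At stake are which patients the primary result describes and which hypothesis its p-value tests.

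**Working it through.** The article gives no SD and no within-patient correlation; Section 3.1 says that none were available. Every SD, correlation and dropout mechanism below is therefore an assumption.

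**1. Complete cases left.** Inputs from Section 3.1: 39 per group, 12% added. 39 × 1.12 = 43.68; the article states 43 (129 in total). With 12% loss, 43 × 0.88 = 37.84, so 37 complete patients per arm, below 39. With 20%, 30% and 40% loss, 34, 30 and 25 per arm remain. The allowance covers 4/43 = 9.3%.

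**2. Which hypothesis is tested.** Assumed: n = 39 per arm, SD 2.2 (variance 4.84), correlation ρ = 0.5, an effect of 1.5 points in one arm only, α = 0.05, noncentral F.

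- *Effect at T2 only, interaction.* λ = n ΣI² / [σ²(1 − ρ)], where I are the interaction effects. ΣI² = 1.5² × (2/3) × (2/3) = 1.0, so λ = 39 / (4.84 × 0.5) = 16.1 on 4 and 228 df. Power is 91%.
- *Effect at T2 only, T1–T3 change.* All arms have the same mean change, so λ = 0 and the rejection rate is 5%.
- *Effect at T3 only, group main effect.* The three-visit average shrinks 1.5 to 0.5. λ = 39 × (0.5² × 2/3) / [4.84 × (1 + 2 × 0.5)/3] = 6.5/3.23 = 2.0 on 2 and 114 df. Power is 22%.
- *Effect at T3 only, T1–T3 change.* λ = 39 × (1.5² × 2/3) / [4.84 × 2 × (1 − 0.5)] = 58.5/4.84 = 12.1. Power is 88%.

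So a significant interaction need not concern the primary outcome, and the group main effect can miss an effect that is on the primary outcome.

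**3. Bias from using complete cases.** Simulation with 300,000 patients per arm, SD 2.2, correlation parameter 0.6 (exchangeable or autoregressive), true T1–T3 difference −1.0, T3 loss of about 10% to 17% per arm.

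| Loss depends on | Mechanism in the arms | Complete cases | Method valid under missing at random |
|---|---|---|---|
| observed T1–T2 worsening | alike | −0.96 to −0.98 | −1.01 |
| observed T1–T2 worsening | different | −0.79 to −1.17 | −0.99 to −1.01 |
| unseen T3 worsening | alike or different | −0.56 to −1.31 | −0.77 to −1.17 |

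In the first two rows an all-available estimate with independence working correlation, as in simple GEE, gives −0.92 to −1.07.

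A second simulation with no true effect used intercept SD 2, slope SD 1 per interval and residual SD 1.2. Loss depended on T2 pain in one arm and was random in the other. Complete-case bias was 0.11 to 0.28 points, and a likelihood-type estimate using T2 was within 0.002 of zero. For scale, with SD of change 2.6 and 37 completers per arm, SE = 2.6 × √(2/37) = 0.60. The bias is then 0.2 to 0.5 SE, and the two-sided type I error about 5.4% to 7.5%.

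**4. Precision from baseline adjustment.** With equal variances the residual variance is 2(1 − ρ)σ² for change and (1 − ρ²)σ² for baseline-adjusted analysis; their ratio is (1 + ρ)/2.

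- ρ = 0.5: 0.75, a 25% reduction.
- ρ = 0.8: 0.90, a 10% reduction.

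With the second simulation's parameters, Var(T1) = 4 + 1.44 = 5.44, Var(T3) = 4 + 4 + 1.44 = 9.44 and Cov = 4. The change variance is 5.44 + 9.44 − 8 = 6.88. The adjusted variance is 9.44 − 16/5.44 = 6.50, a 5.5% reduction.

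**The case against.** The strongest reply is that much of the harm is inferred. A reader might conclude that the article prescribes a complete-case analysis and drops patients who die or progress. It says neither. Exclusion follows from the classical form of the method; a patient who progresses but attends every visit stays in, and the GEE branch can use all observed visits. A missing-data rule or analysis set may sit in a document not shown, so its absence is no fault. The limitations sentence names death as a cause of loss, but uncontrolled pain can be read there as a separate limitation. Section 2.3 also excludes patients whose progression limits outpatient mobility.

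A reader might also infer that the analysis ignores the T1–T3 endpoint. That is too strong: T1 and T3 are both in the model, the interaction contains the contrast, and Table 3 lists change from baseline. Nor is it an error to treat T1 as a response. In randomized arms a comparison of change is unbiased, and baseline adjustment is a matter of precision.

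The bias figures need dropout that works differently by arm, which nothing in the article establishes. All arms have the same visits and reminders. A mixed model also stays biased when loss depends on unseen T3 pain, and after a death it implicitly extrapolates pain scores.

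All of this stands and limits the claim. It does not rescue the stated method. The normality trigger remains undefined and irrelevant to attrition, the ANOVA remains a poor fit to the expected losses, and no contrast is named. The misnamed response variable and the paired groups are drafting slips, since Section 2.6 and Table 3 identify the outcome, but they stand in the only analysis text.

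**Conclusion.** The point holds as a badly chosen and incompletely specified stated method. It is not a finding about missing detail, and it does not show that the result will be biased. The switch makes the primary analysis depend on the data. The classical ANOVA discards partly observed patients in a trial that expects high attrition. The stated tests do not isolate the T1–T3 between-group difference in worst pain.

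The sizes are illustrative. Complete-case bias is near zero when dropout works alike in the arms (at most 0.04 points in the runs with loss driven by observed worsening) and about 0.1 to 0.3 points when it differs. The precision gain over a change score is about 5% to 25%, depending on the unknown correlation and variances. The mismatch between the omnibus tests and the endpoint is structural; only the power figures rest on assumed inputs. The point should be fixed, but it does not undermine the trial.

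**What to change.** Rewrite Section 3.2 around one primary analysis, used whatever the normality result:

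- A linear mixed model for BPI worst pain at T2 and T3, with T1 worst pain as covariate, group, visit and group-by-visit, unstructured covariance and REML.
- All randomized patients with post-baseline data, in their allocated arm. A patient seen at only one of T2 and T3 then still contributes.
- The T3 group contrast as the primary test, naming the arms it compares.
- No switch between ANOVA and GEE.
- Worst pain as the response variable, and independent randomized groups in place of paired ones.

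Because this model is valid only if losses are missing at random, add a sensitivity analysis for outcome-related loss. How deaths are handled in it is for the trial team to decide and state beforehand; assigning worse scores after death is one debatable option.

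The cost is revised wording and a little more analysis work. SPSS can fit the model, and no extra patients, visits or measurements are needed.

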## 4. Discussion

The present study proposes a differentiated approach, utilizing immersive virtual reality exclusively in the office as a tool for introducing and training in mindfulness, followed by home practice using 2D video. This approach aims to explore whether immersive virtual reality can aid in treatment adherence, reduce adverse events, and extend therapeutic effects beyond immediate analgesia. It is hoped that this will contribute to the debate on the existence of evidence supporting the incorporation of virtual reality as an educational and adjuvant resource in oncological palliative care [22].

The protocol proposed here stipulates that cancer patients in palliative care are responsible for maintaining the practice at home. According to the literature, the feasibility of meditation in virtual reality shows that adherence is higher when sessions are conducted in a supervised environment, while home practice presents a higher risk of abandonment [22,23]. In the context of palliative care in oncology, these factors assume even greater relevance, given that fatigue, clinical frailty, and adverse treatment effects can impede the continuity of the protocol, thereby constituting a methodological limitation [24].

Virtual reality (VR)-based non-pharmacological interventions (NPIs) for chronic pain produced reductions in pain intensity that, although they achieved minimal clinical significance in some outcomes, were not superior to equivalent multimedia applications on 2D screens [22]. These results partially contrast with the hypotheses of the present study, which proposes the use of immersive VR exclusively in an outpatient setting as a teaching and initial engagement tool for the practice of mindfulness meditation, which is subsequently performed at home through 2D videos.

Unlike the predominantly cognitive-distraction approach of comparative study, the approach delineated in this study seeks to evaluate the feasibility of virtual reality (VR) as a medium for facilitating learning and adherence to guided meditation, while exploring its potential therapeutic effects beyond immediate analgesia. By combining the immersive experience in the doctor’s office with regular mindfulness practice at home, the study examines whether this approach may be associated with more sustained outcomes in cancer-related pain, quality of life, and psychological morbidity (anxiety and depression).

While the existing literature demonstrates the benefits of VR in chronic pain contexts, with significant reductions in pain intensity, psychological distress, and functional disability, the present protocol seeks to expand this discussion of evidence to a scenario that has been little explored: cancer pain in palliative care [25,26].

Another aspect to consider is the emotional and psychological state of patients. Evidence indicates that emotional distress acts as a modulator of pain perception and response to non-pharmacological interventions [9]. Meditation can promote significant improvement in quality of life, as demonstrated even in populations with high psychological morbidity [10,23]. However, for these benefits to remain consolidated, continuous practice is essential, which makes adherence a critical variable.

Moreover, the extant literature acknowledges that in randomized trials, equivalence of duration between groups is not a methodological requirement. Consequently, these groups are capable of participating in sessions of varying durations, as the duration of interventions is no longer regarded as a limitation, in contrast to conventional mindfulness programs [26]. Studies have demonstrated that there are no substantial discrepancies between the short-term and long-term consequences of interventions that utilize brief meditation techniques to enhance well-being [27].

This scenario should be carefully considered in the final analysis of the results, since differences observed between modalities may reflect both the intrinsic effectiveness of each meditation format and the ability of each patient to maintain the proposed practice. Future research should explore strategies to optimize adherence, such as active remote support, hybrid sessions (in person and at home), or personalized adaptations to the patient’s clinical profile.

It is important to note that this protocol is vulnerable to certain limitations, particularly in cases involving patients receiving palliative care in the terminal phase of the disease. These limitations may include loss to follow-up due to death, the emergence of uncontrollable pain from disease progression, and the combination of pharmacological therapies such as chemotherapy, which can cause side effects and symptoms that are complex to manage.

## 5. Conclusions

The expected results from this protocol have the potential to provide robust evidence for the incorporation of mindfulness meditation as a complementary tool in pain management in palliative care, contributing to the strengthening of the integration of non-pharmacological interventions into established clinical practices. Furthermore, the meticulously outlined methodology in this study can serve as a reference for future research, fostering scientific reproducibility, adaptation to different healthcare contexts, and the continuous improvement of digital interventions applied to palliative care.

## Figures and Tables

**Figure 1 healthcare-14-00266-f001:**
[figure not shown]
Flowchart of the experimental design.

**Table 1 healthcare-14-00266-t001:** Temporal implementation of the experimental protocol.

Planning (0–1 Year)	Intervention (1–2.5 Years)
Questionnaire preparation Definition of criteria Patient selection Randomization and sample size Group allocation	Informed consent (TCLE) Initial questionnaire Assessments at 3 time points Meditation protocol Edmonton Symptom Scale

**Table 2 healthcare-14-00266-t002:** Descriptive table of the experimental groups; time of the experimental protocol; and instruments applied.

Group	Time	Study Assessment Instruments
Case group (Group A) Virtual reality/3D (VR)	Time 1 (T1)—First Day of Intervention	
	Before Meditation	Sociodemographic and clinical questionnaire McGill Quality of Life Questionnaire [17] Brief Pain Inventory (Short Form) [18] Hospital Anxiety and Depression Scale [19] The Edmonton Symptom Assessment Scale (ESAS) [20] The National Comprehensive Cancer Network^®^ (NCCN) [21]
	After Meditation	The Edmonton Symptom Assessment Scale (ESAS) [20]
Active Control Group (Group B) Guided Meditation 2D Video	Time 2 (T2)—Four Weeks After T1	
	Before Meditation	McGill Quality of Life Questionnaire [17] Brief Pain Inventory (Short Form) [18] Hospital Anxiety and Depression Scale [19] The Edmonton Symptom Assessment Scale (ESAS) [20] The National Comprehensive Cancer Network^®^ (NCCN) [21]
	After Meditation	The Edmonton Symptom Assessment Scale (ESAS) [20]
Passive Control Group (Group C) Audio-guided meditation—Audio for breathing exercises	Time 3 (T3)—Eight Weeks After T1	
	Before Meditation	McGill Quality of Life Questionnaire [17] Brief Pain Inventory (Short Form) [18] Hospital Anxiety and Depression Scale [19] The Edmonton Symptom Assessment Scale (ESAS) [20] The National Comprehensive Cancer Network^®^ (NCCN) [21]
	After Meditation	The Edmonton Symptom Assessment Scale (ESAS) [20]

**Table 3 healthcare-14-00266-t003:** Overview of outcome measures and analytical framework.

Outcome	Measurement Variable	Analysis Metric	Aggregation Method	Time Points
Primary outcome	BPI: “worst pain in the last 24 h” (0–10)	Change from baseline; final value	Mean (SD); mean difference	T1, T2, T3
Psychological morbidity	HADS total and subscales	Change from baseline	Mean (SD)	T1, T2, T3
Quality of life	McGill Quality of Life Questionnaire scores	Change from baseline	Mean (SD)	T1, T2, T3
Symptom burden	ESAS total score and individual items	Immediate post-session change and longitudinal change	Mean (SD)	T1, T2, T3
Pain-related symptoms	BPI severity and interference subscales	Change from baseline	Mean (SD)	T1, T2, T3
Adherence	Percentage of completed meditation sessions	Proportion	Mean proportion	Summary at T2 and T3

